### Who will take informed consent? {26a}

Participants will be approached on the hospital ward and given verbal explanation of the study by a study researcher, in most cases an endocrinologist or endocrinology specialist trainee doctor. A written participant information and consent form will be provided. Participants will be informed that their decision whether or not to participate in the study will not impact their access to routine care. Participants will be given the opportunity to read, discuss with support people and ask questions. Those willing to participate will sign the consent form.

For those patients who lack capacity to consent for themselves, the surrogate medical treatment decision maker will be identified and approached in person or by phone, and provided with the written participant information and consent form to assess and sign or not on behalf of the participant. Participants for whom consent is obtained from a medical treatment decision maker will be reassessed every 24 h. If the patient develops capacity to consent they will be provided with a continue to participate consent form and asked whether they consent to continuing to participate in the study.

### Additional consent provisions for collection and use of participant data and biological specimens {26b}—if applicable

Blood and urine biochemistry results will be derived from samples taken as part of routine hospital care. An additional sub-study is planned evaluating serum copeptin levels on day 1 and day 4, with serum samples be collected and stored for analysis with patient permission.

### Interventions

#### Explanation for the choice of comparators {6b}

We seek to determine the utility of tolvaptan in real-world practice through comparison with current standard therapy. While the original SALT trials of tolvaptan were placebo-controlled, these were conducted in ambulatory patients with chronic mild-moderate hyponatraemia (serum sodium 125–135 mmol/L) [11]. The choice of placebo or no intervention would not be a clinically useful or ethical comparison in our population of interest with moderate-to-profound hyponatraemia, as it may risk harm in these patients by delaying treatment.

To reflect real-world practice and for safety, both tolvaptan and fluid restriction will be titrated according to a protocol that allows for escalation and de-escalation of treatment according to serum sodium response in a pre-specified manner.

Tolvaptan (Samsca) is a selective vasopressin V2-receptor antagonist. It is approved in Australia for treatment of clinically significant hypervolaemic or euvolaemic hyponatraemia (serum sodium less than 125 mmol/L, or less marked hyponatraemia that is symptomatic and has resisted correction with fluid restriction) including patients with heart failure and syndrome of inappropriate antidiuresis (SIAD) [13]. In Australia, Tolvaptan is supplied by Otsuka Australia Pharmaceutical Pty Ltd. Detailed pharmacodynamic information, pharmacokinetic information, adverse effects, contraindications and warnings are available in Additional file 3: Appendix 3.

The SALT trials of Tolvaptan versus placebo utilised an escalating dose protocol, with initial dose 15 mg able to be increased to 30 mg then 60 mg in the event of inadequate initial response [11]. The proportion of patients requiring higher doses was not reported. We have chosen a lower starting dose of tolvaptan 7.5 mg in line with post-marking observational studies that have shown reduced rates of serum sodium rise > 12 mmol/24 h with this lower dose [17–19, 25]. While use of an even lower dose of tolvaptan 3.75 mg has been reported [15], the triangular shape in Australia of the lowest-available 15-mg tablet means that it cannot be accurately quartered, leading to selection of 7.5 mg as our starting dose to balance safety, efficacy and practical considerations.

Fluid restriction is the standard initial therapy for euvolaemic hyponatraemia, supported by international guidelines [4, 7]. While the quantity of fluid restriction is not always specified, an initial fluid restriction limit of 1.0 L (1000 ml) per 24 h is evidence-based [26]. Titration of the fluid restriction, in the form of pre-specified reduction in fluid restriction limit if sodium correction targets are not met, has been included in this protocol to reflect current clinical practice and ensure adequacy of treatment. US recommendations suggest down-titration of fluid restriction to 500 ml below 24-h urine output [4] and there is evidence for use of fluid restrictions in the range of 500–1000 ml [27]. We have opted for sequential restriction limits of 750 ml, 500 ml or 0 ml per 24 h total fluid intake for consistency.

#### Intervention description {11a}

Tolvaptan or fluid restriction will be administered and titrated according to serum sodium response (Table 1). In the tolvaptan group, the initial dose will be 7.5 mg, and in the fluid restriction group, the initial total fluid restriction will be 1000 mL.

**Table 1 Tab1:** Dosing protocol for study interventions

DAY	Serum sodium	Prior 24 h sodium increment (mmol/L)	Tolvaptan (TOL) Group	Fluid Restriction (FR) Group	Sodium normalised protocol (both groups)
**1**	115–130		7.5 mg	1000 mL	
**2**	> 134	Any	➔	➔	1500 mL fluid restriction^a^
	≤134	> 8	Nil^b^	Nil^b^	
		5–8	7.5 mg	1000 mL	
		0–4	15 mg	750 mL	
		< 0	30 mg	500 mL	
**3**	> 134	Any	➔	➔	1500 mL fluid restriction^a^
	≤134	> 8	Nil^b^	Nil^b^	
		5–8	Same as D2	Same as D2	
		0–4	Dose increment^c^	FR increment^c^	
		< 0	Dose increment^c^	FR increment^c^	
**4**	Usual care after morning blood test including repeat serum sodium 30 days after discharge.				

^a^All participants regardless of group assignment with Na > 134 mmol/L on day 2 or on day 3 will receive a 1500-mL fluid restriction that day and no other intervention unless the Na increment was > 8 mmol/L over the preceding 24 h in which case they will not receive fluid restriction or tolvaptan

^b^Participants with Na increment > 8 mmol/L over the preceding 24 h will not receive a fluid restriction or tolvaptan for that day, regardless of group assignment

^c^Stepwise dose/fluid restriction increments:

• Tolvaptan: 7.5 mg ➔ 15 mg ➔ 30 mg ➔ 60 mg

• Fluid restriction: 1000 mL ➔ 750 mL ➔ 500 mL ➔ 0 mL

Subsequent daily study visits will evaluate the change in serum sodium over the previous 24 h, reassess volume status and then determine the dosage of tolvaptan or the limit of fluid restriction for that study day, depending on allocation. Early morning bloods will facilitate morning decision-making. Participants whose sodium level increases at the desired rate 5–8 mmol/L over 24 h will continue the same dose of their intervention. Participants whose serum sodium rise is below target will have escalation of intervention—either tolvaptan dose increase (e.g. from 7.5 to 15 mg), or reduction of fluid restriction limit (e.g. 1000 to 750 mL). Participants with decreased serum sodium despite their initial intervention will have more rapid escalation of intervention dosing (e.g. tolvaptan from 7.5 to 30 mg; or fluid restriction from 1000 to 500 ml). Participants who record a 24-h serum sodium rise > 8 mmol/L (or have required intravenous dextrose due to Na > 8 mmol above target during the 24-h period) will not receive either tolvaptan or fluid restriction the following day. Participants who achieve normalisation of serum sodium concentration (135 mmol/L or above) during the course of the trial from either arm will default to a 1500 mL ‘maintenance’ fluid restriction, unless the rise in serum Na was > 8 mmol, in which case they will have free fluid intake.

Tolvaptan doses will be administered prior to 1200 (ideally prior to 1000) to allow safe monitoring of effect during daytime hours with serum sodium measurement 6 and 12 h post dose.

Direct sodium measurement from venous blood gas samples will be preferred to determine outcomes and treatment decisions, unless this is not available. In the setting of glucose levels > 10 mmol/L (> 180 m/dl), a correction factor will be applied according to the formula published by Hillier and colleagues in 1999 (Fig. 1) [24], as endorsed by the European hyponatraemia guidelines [7]. This formula adds 2.4 mmol/l to the measured serum sodium concentration for every 5.5 mmol/L (100 mg/dl) incremental rise in serum glucose. For glucose levels below 10, this amounts to correction by 1 mmol/L or less, therefore for we have chosen to implement this correction for glucose > 10 mmol/L only for practical purposes.

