#### Criteria for discontinuing or modifying allocated interventions {11b}

Overcorrection will be defined according to the European guidelines as an increment in plasma sodium of > 10 mmol/L in 24 h [7]. Overcorrection will be defined as a serious adverse event (SAE) and will prompt individualised management by the treating medical team in collaboration with the endocrinology consult service for decisions regarding re-lowering of plasma sodium with intravenous 5% dextrose therapy.

If the serum sodium rise has not exceeded 10 mmol/L in 24 h but is rising at a faster than desired rate, prophylactic intravenous 5% dextrose will be administered, per protocol. In the event that sodium concentration rises by > 6 mmol/L within 6 h of tolvaptan, or > 8 mmol/L within 12 h of tolvaptan administration, this will be initiated at a rate to match urine output, with increased frequency of sodium monitoring (Table 2) in accordance with safety advice issued by Otsuka Australia Pharmaceutical [28]. This infusion will be discontinued if the plasma sodium then falls back within the target range, and serial sodium monitoring will continue as standard protocol.

**Table 2 Tab2:** Thresholds for intervention with intravenous dextrose 5% in the context of sodium rise following tolvaptan dose

Rise in serum sodium	Time post-tolvaptan	Action
> 6 mmol/L	Within 6 h	Commence IV dextrose 5% at rate equivalent to urine output, continue to monitor frequently and cease when sodium back within target range
> 8 mmol/L	Within 12 h	
> 10 mmol/L	Within 24 h	Aim for re-lowering with bolus hypotonic fluid

In the event that daily bloods are not available for any reason, management will revert to a 1.5-L fluid restriction for both groups while awaiting further results.

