#### Treatment questionnaire

Once allocation has occurred according to the randomization process, a daily treatment questionnaire will monitor progress and assist in implementation of the titration protocol (Tables 1 and 2). Daily biochemistry and 24-h sodium increment will be recorded to determine the intervention for the following 24 h. Details of any potential adverse events, including requirement for intravenous dextrose to mitigate serum sodium rise, are recorded as escalated as required.

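### The hold on tolvaptan after IV dextrose is in the dosing text but missing from Table 1, and after the 6-h trigger neither stops escalation on an increment that dextrose has lowered

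*Protocol article*

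**What the plan says.** Three places in the Protocol article bear on what a tolvaptan participant receives the morning after IV dextrose.

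- **Dosing text, Intervention description {11a}.** Treatment is withheld the next day after a 24-h rise above 8 mmol/L, and, as a separate alternative, for those who "or have required intravenous dextrose due to Na > 8 mmol above target during the 24-h period". A 24-h rise of 5–8 mmol/L keeps the same dose. Below that, "Participants whose serum sodium rise is below target will have escalation of intervention".
- **Table 1, same section.** The dose is set by morning sodium and the prior 24-h increment. Footnote b holds treatment on the increment alone: "Participants with Na increment > 8 mmol/L over the preceding 24 h will not receive a fluid restriction or tolvaptan for that day". Footnote a gives a participant with sodium above 134 mmol/L a 1500 mL restriction and "no other intervention unless the Na increment was > 8 mmol/L over the preceding 24 h". Dextrose appears in no row, column or footnote.
- **Criteria for discontinuing or modifying allocated interventions {11b} and Table 2.** Dextrose starts if sodium "rises by > 6 mmol/L within 6 h of tolvaptan, or > 8 mmol/L within 12 h of tolvaptan administration". It stops once sodium is back in the target range. No rule for the next day's dose follows. Rises above 10 mmol/L in 24 h are handled separately as overcorrection.

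The Treatment questionnaire section says that the daily form will "assist in implementation of the titration protocol (Tables 1 and 2"), and then: "Daily biochemistry and 24-h sodium increment will be recorded to determine the intervention for the following 24 h". The form also records "requirement for intravenous dextrose to mitigate serum sodium rise", but the section does not name this as an input to dosing.

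**The concern.** Dextrose given under Table 2 is meant to pull the sodium rise back, so it changes the number from which the next dose is chosen. A dosing rule that looks only at the morning increment cannot tell a participant who rose slowly from one who rose fast and was rescued. The authors evidently saw this, because the dosing text adds dextrose as its own reason to hold. That reason did not reach Table 1, its wording fits neither dextrose trigger, and it leaves out most participants who meet only the 6-h trigger.

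At stake is whether, and at what dose, tolvaptan is given to someone who has just shown a fast response. The main safety outcome (Outcomes {12}, Table 3) is above-target correction leading to treatment such as IV dextrose, so the re-dosing rule after dextrose should have one meaning. Table 2 is framed around tolvaptan doses, so the problem lies in the tolvaptan arm.

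**Working it through.** The plan states no figure on this point, so there is none to reproduce. The check applies the printed rules to worked cases in whole mmol/L.

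**Inputs.** Eligible baseline 115–130 mmol/L, or 16 whole values (Eligibility criteria {10}). Day 1 dose 7.5 mg. Day 2 rules from Table 1: increment above 8, nil; sodium above 134, 1500 mL; otherwise 5–8 gives 7.5 mg, 0–4 gives 15 mg, below 0 gives 30 mg. Dextrose triggers from Table 2. Target rise 5–8 mmol/L per 24 h from the dosing text.

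**Step 1: what the dextrose clause means.** Taken literally, 8 mmol above a 5–8 target is a rise above 5 + 8 = 13 to 8 + 8 = 16 mmol/L. Both exceed the overcorrection threshold of 10, so the clause would miss the 12-h trigger altogether. Read as a rise above 8 mmol/L, it covers the 12-h trigger and any 6-h rise above 8. That reading is used below.

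**Step 2: a rise of 9 by 12 h, dextrose given.**

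| Morning 24-h increment | Dosing text | Table 1, day 2, sodium ≤ 134 |
|---|---|---|
| 9 | hold | hold |
| 5–8 | hold | 7.5 mg |
| 0–4 | hold | 15 mg |
| below 0 | hold | 30 mg |

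A fall of 9 − 8 = 1 mmol/L is enough to separate the two. At an increment of 8, sodium is 134 or lower for baselines up to 134 − 8 = 126. Table 1 therefore gives 7.5 mg at 115–126 (12 of 16 values) and the 1500 mL restriction at 127–130 (4 of 16). In that second group neither source gives tolvaptan. They differ only over the restriction, and the text's own sentence on normalised sodium also turns on the rise alone, so this limb is the weaker one.

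**Step 3: a rise of 7 or 8 by 6 h, dextrose given, no later rise above 8.** The text's dextrose clause does not apply, and text and table give the same answer.

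- Increment 5, 6, 7 or 8: 7.5 mg is repeated for baselines up to 134 − 5 = 129, 128, 127 and 126 respectively. Above those, the rule for sodium above 134 stops tolvaptan.
- Increment 0–4: 15 mg, twice the day 1 dose, at all 16 baselines, because 130 + 4 = 134 is not above 134.
- Increment below 0: 30 mg.

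Reaching +4 needs a fall of 7 − 4 = 3 or 8 − 4 = 4 mmol/L. Dextrose stops once sodium is back in target, so a repeat dose is the more likely result and escalation the less likely one.

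**Step 4: day 3.** An increment of 5–8 repeats the day 2 dose, which may already exceed 7.5 mg. An increment of 4 or less moves one step up (15 to 30 mg, or 30 to 60 mg). Dextrose again plays no part in Table 1.

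The counts above are of baseline values, not of participants.

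**The case against.** The best reply is that text and table belong to one section and can be read together: an explicit extra stop rule supplements a summary table, and nothing in Table 1 says to dose despite dextrose. Further, Table 1 does not say that its increment is net. The word is also used in {11b} for a rise within 24 h, so +9 at 12 h could count as above 8 and be held under footnote b as well. Both readings are possible, and either would settle Step 2 in favour of holding. Neither is secure. The text lists dextrose separately from the 24-h rise, which would be largely redundant if the increment meant the peak. The Treatment questionnaire section names biochemistry and the 24-h increment as what sets the next dose. Neither reading repairs the clause's wording, and the supplementary reading leaves Step 3 untouched.

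Safeguards exist: sodium checks 6 and 12 h after each dose, daily clinical review, the treating team's right to withdraw a participant, and the Data and Safety Monitoring Board. They limit harm, but none is a re-dosing rule for rises of 10 or less, and the post-dose checks act only once the next dose is in. The full protocol and the REDCap form are not shown and may be clearer. Even so, the article prints both rules, and they do not match.

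Two parts of the objection stand in full. Table 2 dextrose below 10 mmol/L is run to match urine output rather than to re-lower sodium actively, so a fall to +4 or less would not be typical. And repeating 7.5 mg when the day ends at 5–8 is a clinical choice, not an error.

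**Conclusion.** The point holds in limited form and should be fixed. First, when dextrose was given for a rise above 8 mmol/L and the morning increment is 8 or less, the dosing text says hold. Table 1, read on that increment, gives tolvaptan at sodium 134 or lower, or a 1500 mL restriction above that. Second, after a 6-h rise above 6 but not above 8, neither text nor table stops escalation at a morning increment of 4 or less, although dextrose helped to lower that value.

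This rests on reading the clause as a rise above 8, on reading Table 1's increment as the morning value, and on whole-number sodium.

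A reader might infer that text and table always give opposite orders after the 12-h trigger. They do not: they agree if the increment stays above 8, and neither gives tolvaptan if morning sodium is above 134. A reader might also infer that rescued participants would routinely have their dose doubled, or that the primary comparison is biased. The document gives no rate for these events, and no effect on the primary endpoint or power has been shown.

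**What to change.** 1. In the dosing text, replace the dextrose clause with: *or received IV dextrose under Table 2 for a rise > 8 mmol/L during the 24-h period*.
2. Add the same condition to Table 1 footnotes a and b, so that neither tolvaptan nor fluid restriction is given that day whatever the morning increment.
3. Add a Table 1 footnote: tolvaptan is not escalated on a 24-h increment during which IV dextrose was given under Table 2. This leaves the same dose available after the 6-h trigger.
4. Use the dextrose item already recorded in the daily questionnaire as an input to titration.

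The cost is a short ethics amendment, notice to the Data and Safety Monitoring Board and study personnel, and one added rule in the REDCap titration form. No new data are collected. The downside is that a few tolvaptan participants miss a dose or an escalation, which may slightly slow correction in those whose sodium has fallen back. That touches the worry about delayed treatment raised under Explanation for the choice of comparators {6b}.

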### Eligibility criteria {10}

Inclusion criteria:
Serum sodium 115–130 mmol/L on direct sodium measurement (venous blood gas), corrected for glucose level if glucose > 10 mmol/L [24]Age 18 years or overInformed consent (patient, or medical treatment decision maker)

Exclusion criteria:
Hypovolaemia as defined as either:
Clinical impression of hypovolaemia; orUrine sodium < 20 mmol/L (or urine chloride < 10 mmol/L in the presence of metabolic alkalosis) in the absence of pitting oedema.Polydipsia/polyuria, defined by first collected urine sample specific gravity < 1.003Severe symptoms of hyponatraemia warranting hypertonic saline:Vomiting (not attributable to other cause)Coma, defined by GCS < 8 on day 1 of admissionDeep somnolence, defined by sedation score > 1 on day 1 of admissionSeizure at any time in admissionRespiratory arrest at any time in admissionThiazide or thiazide-like diuretic use within preceding 5 daysRisk factors for osmotic demyelination syndrome:
Malnutrition (BMI < 16 or other clinical concern)Alcohol abuse (> 14 standard drinks per week)Child-Pugh B or C CirrhosisHypokalaemia (≤ 3.0 mmol/L) on day 1, or need for intravenous potassium replacementIncrement in serum sodium from baseline to day 1 of > 0.5 mmol/L/h or > 10 mmol/L/24 hOther potential endocrine cause of hyponatraemia:
Untreated glucocorticoid deficiency or mineralocorticoid deficiency (evaluated with serum cortisol level, in context of clinical history and concurrent medications)Significant hypothyroidism (TSH > 20 IU/L, and/or free T4 < 6 pmol/L)Chronic kidney disease stage 5 (estimated glomerular filtration rate (eGFR) < 15 ml/min/1.73 m^2^ or renal replacement therapy)Systolic blood pressure < 100 mmHgInability to drink fluid unaidedPregnancy (by history, confirmed if necessary by serum *β*HCG) or breastfeedingMarked hyperglycaemia (day 1 venous blood gas glucose > 30 mmol/L)

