**Fig. 1 Fig1:**

Formula for correction of sodium in the presence of hyperglycaemia, to be implemented when glucose > 10 mmol/L (> 180 mg/dL) [24]

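### The glucose correction left out below 10 mmol/L reaches about 2 mmol/L (assumed reference 5.5), not 1 or less, so correcting one of two readings can distort a 24-h sodium increment

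*Protocol article*

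**What the plan says.** The slope of the correction is given in Intervention description {11a}: "This formula adds 2.4 mmol/l to the measured serum sodium concentration for every 5.5 mmol/L (100 mg/dl) incremental rise in serum glucose". The next sentence justifies the cut-off: "For glucose levels below 10, this amounts to correction by 1 mmol/L or less, therefore for we have chosen to implement this correction", which it then limits to glucose above 10 mmol/L on grounds of practicality. The formula itself, including the reference glucose from which the rise is counted, is in Fig. 1.

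The sodium value concerned is used widely. The same section says "Direct sodium measurement from venous blood gas samples will be preferred to determine outcomes and treatment decisions" and then adds the glucose correction. Eligibility criteria {10} takes sodium "corrected for glucose level if glucose > 10 mmol/L". The Treatment questionnaire section says "Daily biochemistry and 24-h sodium increment will be recorded to determine the intervention for the following 24 h", and a footnote to Table 1 says "Participants with Na increment > 8 mmol/L over the preceding 24 h will not receive a fluid restriction or tolvaptan for that day". The discontinuation section {11b} sets the safety label: "Overcorrection will be defined according to the European guidelines as an increment in plasma sodium of > 10 mmol/L in 24 h". That last sentence does not say whether the glucose-corrected value is meant.

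**The concern.** The sentence offers the size of the omitted correction as the reason why leaving it out is harmless. If the true size is about twice that, the reason given for placing the cut-off at 10 is wrong.

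The practical consequence lies in differences between readings. Titration runs on 24-h increments, in whole-number rows (below 0, 0–4, 5–8, above 8). If one morning's glucose is just above 10 and the other's just below, one sodium is raised by about 2 mmol/L and the other is left alone. The increment then contains a change that the participant's sodium did not make. At stake are single dosing decisions and, possibly, single overcorrection labels, which the protocol treats as serious adverse events.

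**Working it through.** **Inputs.** Slope k = 2.4/5.5 = 0.436 mmol/L of sodium per mmol/L of glucose (Intervention description {11a}). Cut-off: glucose 10 mmol/L. Stated maximum below the cut-off: 1 mmol/L. Reference glucose: assumed 5.5 mmol/L, because Fig. 1 was not available. The text pairs 5.5 mmol/L with 100 mg/dL, but that describes the increment and does not settle the reference.

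**The stated figure.** Correction = k × (glucose − reference). At glucose 10:

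- reference 5.0: 0.436 × 5.0 = 2.18
- reference 5.5: 0.436 × 4.5 = 1.96
- reference 6.1: 0.436 × 3.9 = 1.70
- reference 7.0: 0.436 × 3.0 = 1.31

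In mg/dL with a reference of 100: 2.4 × (180 − 100)/100 = 1.92. The stated maximum is not reproduced. It requires a reference of at least 10 − 1/k = 7.71. With reference 5.5 the correction stays within 1 mmol/L only up to glucose 5.5 + 1/k = 7.79; it is 1.53 at glucose 9.

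**Effect on an increment.** When one glucose is above 10 and the other is not, the false change equals the correction omitted from the second reading. It is therefore largest, about 2, when that glucose is just below 10, and smaller further down (0.65 at glucose 7). With reference 5.5 the correction is 2.05 at glucose 10.2 and 1.88 at 9.8. Table 1's rows imply rounding to whole mmol/L, though the protocol does not say so.

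| Measured sodium | Glucose | Rule as written | Both readings corrected | What changes |
|---|---|---|---|---|
| 124 to 130 | 10.2 to 9.8 | 130 − 126.05 = 3.95, rounds to 4 | 131.88 − 126.05 = 5.83, rounds to 6 | On day 2, escalation to 15 mg or 750 mL instead of an unchanged dose |
| 124 to 131 | 9.8 to 10.2 | 133.05 − 124 = 9.05, rounds to 9 | 133.05 − 125.88 = 7.17, rounds to 7 | No treatment that day instead of an unchanged dose |
| 120 to 129 | 9.8 to 10.2 | 131.05 − 120 = 11.05, rounds to 11 | 131.05 − 121.88 = 9.17, rounds to 9 | Overcorrection label only; the Table 1 row is above 8 either way |

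With sodium rounded, the three results are the same for references 5.0, 5.5, 5.6 and 6.1.

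**Which rises are exposed.** For a narrow crossing of 10, the row changes for measured rises of 0–1, 5–6 and 9–10 when glucose falls, and of −2 to −1, 3–4 and 7–8 when it rises. On day 3 the two lowest rows lead to the same action, so shifts around zero matter only on day 2.

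**Single readings.** The same step exists at eligibility. A measured 129 qualifies at glucose 9.9; at 10.1 it becomes 129 + 2.01 = 131.01 and does not.

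**Effect on the primary comparison.** Suppose, purely as an assumption, that 10% of participants carry a 2 mmol/L false change. The added variance is at most 0.10 × 2² = 0.4, against 4.9² = 24.0 from the Sample size section: about 1.7%. At 5% of participants it is about 0.8%.

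**The case against.** The strongest reply is that two things should be kept apart. The wrong figure is a slip in one sentence. The step is a property of any cut-off and would remain if the sentence were corrected, and the protocol openly says that it chose the cut-off for practicality. This stands: the cut-off is not itself an error. What remains is that the increment rule allows one reading to be corrected and the other not, which is avoidable while keeping the cut-off.

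Second, a changed decision needs several things together: glucose crossing 10 between the two readings, a rise close to a row boundary and, for dosing, sodium not yet normalised. The examples were built to meet these conditions. Rounding is inferred; without it, a reference of 6.1 gives 130 − 125.79 = 4.21 in the first example, which falls between two rows. Daily reassessment and sodium checks 6 and 12 h after tolvaptan limit the harm from one mis-stepped dose. All of this stands, and it keeps the point minor.

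Some stronger readings are not supported:

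- A reader might infer that the slope alone yields 2 mmol/L. It does not; a reference glucose is needed as well.
- A reader might infer bias in the treatment comparison. The correction rule is the same in both arms, so noise is the likelier result.
- A reader might infer a tilted safety comparison, because the dextrose thresholds in Table 2 are defined only after tolvaptan. The document does not say that those thresholds use corrected sodium, and gives nothing from which to judge a direction.
- The 2 mmol/L minimally relevant difference is a difference between group means and is no yardstick for an error in one reading.

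**Conclusion.** The stated maximum correction is wrong for any reference glucose below about 7.7 mmol/L. With the assumed reference of 5.5 the omitted correction approaches 1.96 mmol/L just below the cut-off, with a range of 1.70 to 2.18 for references of 6.1 to 5.0. When glucose crosses 10 between readings, the 24-h increment can carry a false change of up to that size, enough to move a participant by one Table 1 row. A changed overcorrection label also requires that corrected sodium be used for that definition, which is inferred from the general statement about outcomes and treatment decisions. Frequency cannot be judged from the document. The effect on the between-group mean is probably small. This is a minor point, but the stated reason is wrong and the remedy is cheap.

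**What to change.** 1. Change the sentence in Intervention description {11a} to say that below glucose 10 the omitted correction is up to about 2 mmol/L, after checking the reference in Fig. 1, and let the cut-off rest on practicality alone.
2. Clarify the increment rule: when either reading of an increment has glucose above 10, correct both.
3. Add a sensitivity analysis of the sodium endpoints and the overcorrection count, with the correction applied continuously above the formula's reference wherever a glucose paired with the sodium is available. This also covers increments with both glucose values below 10, which step 2 leaves uncorrected.

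The cost is a little extra analysis and a minor clarification handled under the protocol amendments section {25}, with ethics approval and notice to the data safety monitoring board and study personnel. Glucose must already be read to apply the present rule, but the Biochemistry section does not list it among the recorded values, so the sensitivity analysis may be incomplete.

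Do not replace the cut-off for eligibility and titration during recruitment. Earlier and later participants would be selected and dosed under different rules, for a gain that cannot be quantified.
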